#### Primary Outcome

*Mental health*: we will use the extent of psychological distress as a measure of mental health. Psychological distress relates to unspecific behavioral, emotional, cognitive, and psychophysiological components of mental health. The Kessler K6 screening scale will be used (33). The K6 has been extensively used in the World Mental Health Survey and has been validated and translated to German. It consists of six items for the measurement of distress during the past 30 days, resulting in a total score ranging between 0 and 24 points. K6 respondents can be classified into three severity groups, with 0–4 points indicating no distress, 4–12 points moderate distress, and 13–24 points high distress (32).

#### Secondary Outcomes

*Well-being*: the last item from the EUROQOL EQ-5D will be used to measure well-being (86). Participants are asked to rate their well-being on a Likert scale ranging from 0 to 100, where 0 represents the worst state and 100 the best state: “*What number between 0 and 100 best describes your well-being today?*”

*Intentions toward help-seeking*: The intention to seek help for a mental health problem will be measured with the General Help-Seeking Questionnaire (GHSQ) (87). The GHSQ asks: “*If you were having a mental health problem, how likely is it that you would seek help from the following source?”* with two help source options: 1. informal source (friend or family) and 2. professional source (general practitioner, mental health service, educational health service). Respondents rate the likelihood of seeking help from each source on a 7-point Likert scale ranging from “extremely unlikely” to “extremely likely.”

*Help-seeking behavior*: help-seeking is defined as the behavior of actively seeking assistance, regardless of whether the source is informal or formal. The Actual Help-Seeking Questionnaire (AHSQ) will be used to measure help-seeking for a mental health problem within the past 4 weeks (88). The AHSQ first asks whether or not any help had been sought for a mental health problem during the reference period. Second, if help had been sought, whether it was sought from an informal source or from a professional source (identical to the help source options of the GHSQ). For each item, a score of one indicates that help had been sought and a score of 0 that help had not been sought.

*User activation*: we refer to user activation as the degree of perceived knowledge, skill, and confidence for the active self-management of one’s mental health condition. The Patient Activation Measure (PAM) will be used, a reliable and validated measure for the degree of activation. The PAM rates the agreement to 13 items on a 4-point scale (89). Respondents are scored on four levels, with a higher score indicating higher activation.

*Attitudes toward mental health services*: Attitudes about the effectiveness of mental health services influence the likelihood of seeking professional help. The Attitudes Toward Seeking Professional Psychological Help Scale-SF (ATSPPH-SF) will be used to measure attitudes toward mental health services (90). The ATSPPH-SF has 10 items rated on a 4-point scale, resulting in a total score ranging from 0 to 30, where higher values represent more positive attitudes. It has shown good validity and reliability (91).

*Perceived stigmatization*: to measure the extent to which participants perceive to be stigmatized due to a mental health problem, we will adapt the stigma domain of the Caregiver Burden Scale (CBS). The CBS was originally developed to assess four domains of stigma among caregivers of family members with mental illness (92). We only use the domain of stigma which has two items: 1: “*having a mental health problem makes my family feel ashamed”* and 2: “*having a mental health problem makes me feel ashamed*.” Respondents rate the items on a 5-point scale (1 = never, 5 = always). Higher scores indicate a higher level of perceived stigma. A composite measure of the stigma perceived will be constructed from the total of the scores for these two questions.

*Smartphone app quality*: to measure the degree to which the smartphone app meets quality criteria from a user perspective, we will use the Mobile App Rating Scale (MARS) from Stoyanov, Hides (93). The MARS has 23 items and rates smartphone app quality along five dimensions: Engagement, functionality, esthetics, information quality, and subjective quality. It has demonstrated excellent internal consistency and inter-rater reliability. The assessment of smartphone app quality will be conducted at post-intervention among all participants who have used one of the study apps.

*Expectations*: to measure credibility of the smartphone application and the user’s expectations toward it, the credibility and expectation questionnaire (CEQ) will be used. The CEQ consists of six items and has demonstrated good psychometric properties (94).

The following objective usage parameters are automatically collected by smartphone application during the study period.

*Engagement*: the extent to which participants are exposed to the intervention and engage with it will be measured by usage metrics of the smartphone application. This includes a date and time-stamped log of when participants open the application and the length of each session. From this information, the number of and length of user interactions with the application will be computed for the 30-day monitoring period. In the intervention group, the users’ engagement with the supportive feedback content will be assessed by tracking the number of received feedback and user ratings of each feedback message (dismiss/remind).

*Adherence*: adherence with outcome assessments will be measured, and in the groups that use self-monitoring, adherence with self-monitoring will be measured. The number of completed daily self-monitoring will be assessed as defined by completion of the last page of an assessment and can range between 0 and 28.

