## Abstract

Mobile health (mHealth) could be widely used in the population to improve access to psychological treatment. In this paper, we describe the development of a mHealth intervention on the basis of supportive self-monitoring and describe the protocol for a randomized controlled trial to evaluate its effectiveness among smartphone users with psychological distress. Based on power analysis, a representative quota sample of *N* = 186 smartphone users will be recruited, with an over-sampling of persons with moderate to high distress. Over a 4-week period, the intervention will be compared to a self-monitoring without intervention group and a passive control group. Telephone interviews will be conducted at baseline, post-intervention (4 weeks), and 12-week follow-up to assess study outcomes. The primary outcome will be improvement of mental health. Secondary outcomes will include well-being, intentions toward help-seeking and help-seeking behavior, user activation, attitudes toward mental-health services, perceived stigmatization, smartphone app quality, user satisfaction, engagement, and adherence with the intervention. Additionally, data from the user’s daily life as collected during self-monitoring will be used to investigate risk and protective factors of mental health in real-world settings. Therefore, this study will allow us to demonstrate the effectiveness of a smartphone application as a widely accessible and low-cost intervention to improve mental health on a population level. It also allows to identify new assessment approaches in the field of psychiatric epidemiology.

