##### Self-Monitoring

During the 28-day intervention period, daily self-monitoring on the basis of AAs will be conducted. The research methodology of AA is well suited to study people in their natural environment, resulting in ecologically valid data from the persons’ everyday life (44). The self-monitoring protocol should detect and monitor micro-processes of mental health and intra-individual variability, as well as the contextual factors in daily life. We aimed to design a brief, but comprehensive protocol for daily self-monitoring of mental health based on self-reports, while attempting to keep participant burden low. The most common areas of psychopathology will be included: Mood, depression, anxiety, stress, sleep, and functional impairment. In addition, physical activity, social activity, daily hassles and daily uplifts, and alcohol and drug use will be monitored as risk and protective factors of mental health. With a total length of 23 items, participants will be able to complete a daily report in under 5 min. All AAs will be time and date stamped.

*Mood*: To self-monitor daily mood, we will use the version of the Multidimensional Mood State Questionnaire (MDBF) from Wilhelm and Schoebi (45). The MDBF was designed specifically for daily life studies with repeated mood ratings, where a parsimonious measure that is sensitive for change is needed. It uses six items to assess the three factors calmness, valence, and energetic arousal in the present moment. Responses are indicated on three separate six-point bipolar scales with the endpoints labeled “very” (“good–bad,” “awake–tired,” and “calm–nervous”).

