### Outcomes

Study outcomes are assessed at four time points: screening (T0), baseline (T1), post-assessment (T3) and follow-up (T4). While the screening (T0) relies on self-assessments collected during participant registration on the study website, structured telephone interviews are conducted at T1, T2, and T3 to assess the primary outcome. The telephone interviews will be conducted by the Academic Survey Lab at the University of Hamburg. Trained interviewers who are blinded to the study condition will conduct the interviews, resulting in an independent outcome assessment to avoid confounding with the self-monitoring data. The secondary outcomes will be self-assessed on the smartphone for all three groups.

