### Statistical Analysis

Before analysis, data will be prepared and cleaned according to the guidance in Ref. (99). Data will then be analyzed according to the recommendations in the CONSORT statement for evaluation of e-health interventions, as well as the mHealth evidence reporting and assessment checklist from the WHO mHealth Technical Evidence Review Group (100, 101). Intention-to-treat analysis (ITT) and additional per-protocol analysis (PP) will be performed, the former including the data of all participants randomized and the latter using only the subset of participants who complete all assessments (T0, T1, T2, T3).

Multilevel models are an appropriate data-analytic strategy for smartphone data, involving daily measurements, resulting in repeated observations nested within individuals (102). These models are well suited to test the general effectiveness of supported monitoring among smartphone users, but also its differential effectiveness and its conditional effectiveness. Models include analysis of both within-person and between-person variance. Missing data will be replaced using Markov Chain Monte Carlo multiple imputation, which is considered to produce more precise estimates of the true intervention in the ITT analysis compared other imputation methods, i.e., last observation carried forward (103).

*General effectiveness*: to test for changes in the outcome variable from before to after the intervention period, repeated-measures analysis of variance (RM-ANOVA) will be conducted for each intervention outcome (104). In the RM-ANOVA, the within-person effect of time is used as an index of general intervention effectiveness. For the analysis of between-person variance, the model can be extended to multivariate analysis of variance (MANOVA). In this case, a between-subjects factor for group membership is added (Supported monitoring group vs. AA group vs. control group). If there is an interaction between the time factor and the group factor, we will conclude that the intervention was effective.

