*Daily life data*: we will compute Cox proportional hazards models to investigate daily life behavior as risk and protective factors of mental health. Cox proportional hazards models are a type of survival model that allows for the estimation of the hazard (or risk) of an event of interest given prognostic variables. We will model changes in mental health as measured by K6 as the outcome event (i.e., improved, maintained, and deteriorated), and separate models will be computed for well-being, intentions to seek help, and help-seeking behavior as outcome event. As risk and protective factors, we will include daily life measures. Risk factors include alcohol and substance use, the frequency of daily hassles, low social activity, and low physical activity. Protective factors include coping behavior, social support, and physical activity. Furthermore, the instability or variability of daily symptoms over the 30-day monitoring period will also be examined as a risk factor by computing within-person variances, first-order autocorrelation, the mean square successive differences, and the probability of acute change according to Jahng et al. (109). Discrimination ability (the ability of the model to separate individuals who develop the event from those who do not) will be assessed with the C statistic. Model calibration, that measure how accurately model predictions match overall observed event rates, will be evaluated with a version of the goodness of fit (110). Internal model validation will be carried out. For all daily life analysis, data from the AA group will be used (*N* = 62).

*Access*: we will describe access to the intervention in terms of population characteristics (sample representativeness), demographics, clinical characteristics, and sample comorbidities using the appropriate descriptive statistics.

*Engagement*: to assess participant engagement, we will examine the proportion of study drop-outs and the proportion of enrolled individuals who respond to the outcome assessments at each time point, and the proportion of daily life assessments filled out during the 30-day interval.

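### A fixed 4-week look-back at the 12-week follow-up leaves at least weeks 4 to 8 of help-seeking behaviour unobserved; a lesser point is RM-ANOVA for this 0/1 outcome

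*Protocol article*

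**What the plan says.** Secondary Outcomes gives the AHSQ a single reference period: it "will be used to measure help-seeking for a mental health problem within the past 4 weeks". Scoring is binary: "For each item, a score of one indicates that help had been sought and a score of 0 that help had not been sought".

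On timing, the Abstract states: "Telephone interviews will be conducted at baseline, post-intervention (4 weeks), and 12-week follow-up to assess study outcomes". The Outcomes section lists the waves: "Study outcomes are assessed at four time points: screening (T0), baseline (T1), post-assessment (T3) and follow-up (T4". It names no wave between post-assessment and follow-up. The same section then uses T1, T2 and T3 for the interviews, so the labels are inconsistent. It assigns the telephone interviews to the primary outcome and has the secondary outcomes self-assessed on the smartphone in all three groups. The Self-Monitoring section fixes the length of the intervention: "During the 28-day intervention period, daily self-monitoring on the basis of AAs will be conducted".

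On analysis, the Statistical Analysis section says that "repeated-measures analysis of variance (RM-ANOVA) will be conducted for each intervention outcome", takes a time-by-group interaction as evidence of effectiveness, and expresses effects as Cohen's d. The only other model that names help-seeking behaviour is the Cox analysis of daily life data, where "separate models will be computed for well-being, intentions to seek help, and help-seeking behavior as outcome event". That analysis uses the AA group alone (N = 62).

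**The concern.** Help-seeking is an event, and a 4-week question cannot see an event that happened earlier than that. With post-assessment at week 4 and the next wave at week 12 or later, there is a stretch after the intervention that no AHSQ question covers.

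The outcome matters to this trial. The Support section says that users with severe symptoms are encouraged to seek professional help and are given contact details, and the Introduction and Discussion rest the rationale on unmet treatment need. A prompt received late in the 28 days may be acted on only after week 4. No later analysis plan can recover contacts that were never asked about.

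The model is a second, smaller matter. RM-ANOVA and Cohen's d are written for every intervention outcome, and so apply to a 0/1 score. Its variance, p(1 − p), changes with the rate, and a standardised mean difference is a poor way to report it.

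**Working it through.** **1. The plan's own figure.** No figure is given for help-seeking. The only sample size is N = 141 before drop-out, for the K6 (Sample Size Calculation). Inputs: d = 0.25, so f = d/2 = 0.125; k = 3 groups; m = 4 waves; r = 0.65 (printed as 65); ε = 0.8; alpha 0.05; power 95%.
- λ = f²·N·m·ε/(1 − r) = 0.015625 × 141 × 4 × 0.8 / 0.35 = 20.14
- df1 = (3 − 1)(4 − 1)(0.8) = 4.8; df2 = (141 − 3)(4 − 1)(0.8) = 331.2
- Power = 0.953. The smallest N is 140, or 141 in three equal groups.

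The figure reproduces. It rests on the K6, so nothing below changes it.

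**2. What the AHSQ windows cover.** An item asked at week t covers weeks t − 4 to t. The article does not say whether the 12 weeks run from baseline or from the end of the intervention, so both readings are shown.

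| | 12 weeks from baseline | 12 weeks from end of intervention |
|---|---|---|
| Post-assessment window | 0 to 4 | 0 to 4 |
| Follow-up window | 8 to 12 | 12 to 16 |
| Not observed | 4 to 8 | 4 to 12 |
| Share of post-intervention time | 4/8 = 50% | 8/12 = 67% |
| Share of time since baseline | 4/12 = 33% | 8/16 = 50% |

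Weeks 4 to 8 are unobserved on both readings.

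**3. From time to contacts.** Suppose contacts after week 4 occur at a constant rate. If each such person makes one contact, the share missed equals the share of time: 50% or 67%. If a proportion q of those whose first post-intervention contact falls in the gap seek help again inside the follow-up window, the share becomes 0.50(1 − q) or 0.67(1 − q). At an assumed q = 0.5 that is 25% or 33%; at q = 1 it is zero. Anyone who also sought help in weeks 0 to 4 is already counted at post-assessment. The documents give neither a rate nor q.

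**4. Whether another measure fills the gap.** Patient history (Other Assessments) covers past service use but has no follow-up schedule. The usage logs record app use, not help sought. The Cox analysis uses one arm and would rely on the same AHSQ data.

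**5. Whether RM-ANOVA misbehaves on the 0/1 item.** The time-by-group test with Greenhouse-Geisser correction was simulated under the null: three groups, three waves, an assumed latent correlation of 0.65, and 4,000 data sets per setting. Rejection at nominal 0.05, with 47 (141/3) and 62 (186/3) per group:

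| Assumed rate | 47 per group | 62 per group |
|---|---|---|
| 2% | 0.023 | 0.031 |
| 5% | 0.039 | 0.043 |
| 10% | 0.044 | 0.041 |
| 20% | 0.053 | 0.040 |
| 30% | 0.042 | 0.053 |

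Simulation error at 0.05 is √(0.05 × 0.95/4000) = 0.0034. There is no inflation. The test is clearly conservative at 2%, slightly so at 5%, and close to nominal from 10% upwards.

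**The case against.** The strongest reply is that the plan defines a status measure with the same window at every wave, which keeps the waves comparable, and that it never claims to measure cumulative help-seeking. The K6, with its 30-day reference period, also skips part of the follow-up interval. The post-assessment window covers the whole 28 days in which users are prompted. There is no AHSQ-specific visit schedule, and the link function for one secondary outcome is the kind of detail a condensed article can leave to an analysis plan.

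Much of this stands. Comparability is a good reason to keep the 4-week item, and help sought while the app is active is captured. The comparison with the K6 is weaker: distress is a state that can be read at follow-up, whereas a contact in week 6 leaves no trace in a question about weeks 8 to 12. The analysis-plan argument covers the choice of model, but not a question that was never asked.

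Several stronger readings are tempting and are not supported:
- A reader might infer that half to two thirds of first contacts will be lost. That needs a constant rate and no repeat contact, and the AHSQ counts informal help from friends or family, where repetition is plausible.
- A reader might infer that the month after the intervention is the peak time for contact. No passage says so, and the gap does not depend on it.
- A reader might infer that the arm comparison is biased. A window applied equally to all arms lowers the event count; it does not by itself distort the comparison within that window. Weeks 4 to 8 lie outside the reference period; they are not miscoded within it.
- A reader might infer that RM-ANOVA gives false positives or no risk difference. The simulation shows no inflation, and cell means of a 0/1 score are proportions, so their contrasts are risk differences.

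**Conclusion.** The gap is real and follows from two stated facts, the 4-week window and the visit times. It covers 4 of 8 post-intervention weeks (50%), or 8 of 12 (67%) if follow-up is counted from the end of the intervention. A participant whose only contact falls there counts as not having sought help at either post-randomisation wave. The share of contacts lost is unknown; under a constant rate the same percentages are its ceiling. The consequence is fewer events and less sensitivity on a secondary outcome that the app directly targets. The primary outcome and the sample size are untouched.

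This assumes that the AHSQ is given at post-assessment and follow-up, as the general statement in Outcomes implies. If it were omitted at follow-up, the gap would be larger.

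The use of RM-ANOVA and Cohen's d is a lesser point of fit and reporting, with some loss of sensitivity if help-seeking is rare. Trial Status places the trial in preparation, so the question can still be changed.

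**What to change.** 1. Keep the 4-week AHSQ item at every wave, for comparability.
2. At follow-up, add one AHSQ item on the smartphone covering the time since the post-assessment. State whether the 12 weeks run from baseline or from the end of the intervention.
3. Define a supplementary endpoint: any help sought from baseline to the 12-week follow-up, positive if either the post-assessment 4-week item or the new item is positive. Name it by visit, because the T-labels conflict.
4. Compare arms on this endpoint by logistic regression adjusted for the baseline 4-week item, and report risk differences.
5. Analyse the repeated 4-week item by GEE or mixed logistic regression in place of RM-ANOVA and Cohen's d.

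The cost is one question at one wave and a change of model. The new item needs a recall of 8 or 12 weeks, and it has no baseline counterpart of equal length. That is why it should supplement the 4-week item and not replace it.

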#### Sample Size Calculation

A power analysis was performed to detect a group difference on the primary outcome at post-assessment group. The calculation is based on the assumption that a difference between the supported monitoring group and either AA group or control group within the margin −0.25 < Cohen’s *d* < 0.25 can be neglected. We assume no difference between the two latter groups. Therefore, a between-group difference of *d* = 0.25 should reach statistical significance as an indicator of the general effectiveness of the intervention. The target sample size was computed using Gpower (40) for a repeated-measures analysis of variance for a within-between interaction of time and group (ANOVA). We used a targeted power of 95%, a significance level alpha of 0.05, four assessment waves, a conservative estimate of correlation between measurements (*r* = 65) and variances of the differences between groups (non-sphericity correction epsilon = 0.8). This results in a total *N* = 141. Adding 20% drop-out at T2 and T3, we will include 186 participants (62 per group).

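### User activation (13-item PAM) is given only a four-level score; read as written, a four-category grade goes into the RM-ANOVA and power is lost for no gain

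*Protocol article*

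**What the plan says.** Under Secondary Outcomes, user activation covers perceived knowledge, skill and confidence in managing one's own mental health. The instrument is described as follows: "The PAM rates the agreement to 13 items on a 4-point scale". The only statement on scoring is "Respondents are scored on four levels, with a higher score indicating higher activation". No total, mean or scaled score is named.

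Under Statistical Analysis (General effectiveness), "repeated-measures analysis of variance (RM-ANOVA) will be conducted for each intervention outcome". A group factor is then added, and the decision rule is: "If there is an interaction between the time factor and the group factor, we will conclude that the intervention was effective".

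Three other multi-item scales do have a stated total. The K6 has 0 to 24, with severity groups described as a further classification. The ATSPPH-SF has 0 to 30, and the stigma items are summed.

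**The concern.** Thirteen items with four response options give 13 × 3 + 1 = 40 possible sum scores. Reducing them to four levels has two effects on a repeated-measures test. It shrinks the standardised group difference, because movement within a level is not seen. It also lowers the correlation between occasions, and that correlation is where the test gets its precision. RM-ANOVA moreover treats the steps between levels as equal intervals.

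At stake is one secondary outcome. It is of some interest because the Introduction and the Support section name better self-management skills as an expected benefit, and the PAM is the instrument closest to that. A real gain in activation would be easier to miss.

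**Working it through.** **Inputs from the article.** Three arms, 1:1:1, 62 per group. "We used a targeted power of 95%, a significance level alpha of 0.05, four assessment waves". Correlation 0.65 (printed as 65), epsilon 0.8, and the effect: "a between-group difference of *d* = 0.25 should reach statistical significance as an indicator of the general effectiveness". All of these are stated for the primary outcome, so using them for the PAM is an assumption.

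**Assumed inputs.** The underlying score is normal. The level frequencies are not in the article, so a range is shown.

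**1. Reproducing the plan's sample size.** For the within-between interaction, λ = f²·N·m·ε/(1 − ρ), df1 = (k − 1)(m − 1)ε and df2 = (N − k)(m − 1)ε. With f = d/2 = 0.125, k = 3, m = 4, ρ = 0.65 and ε = 0.8, N = 140 is the smallest total reaching 95% power; three equal arms make it 141. At N = 141, λ = 0.015625 × 141 × 4 × 0.8/0.35 = 20.14, df = 4.8 and 331.2, and power is 0.953. The stated 141 is reproduced.

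**2. Same formula with four levels.** Multiply f by the correlation between the full score and its level, and replace ρ by the correlation between the four-level scores.

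| Level frequencies (%) | Effect kept | ρ | Power, N = 141 | Loss (points) |
|---|---|---|---|---|
| full score | 1 | 0.65 | 0.953 | – |
| 16/34/34/16 | 0.939 | 0.581 | 0.861 | 9.2 |
| 25/25/25/25 | 0.925 | 0.579 | 0.847 | 10.6 |
| 10/15/35/40 | 0.904 | 0.568 | 0.816 | 13.7 |
| 5/10/25/60 | 0.840 | 0.541 | 0.717 | 23.6 |

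If all 186 are analysed, the loss runs from 4.2 to 14.2 points with four waves (full score 0.990) and from 7.0 to 19.3 with three waves (full score 0.970).

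**3. Direct simulation of the group-by-time test.** Baseline and post scores were drawn with r = 0.65, with a shift d at post in the supported arm only. The test was a one-way ANOVA on change, run on the full score and on the four-level score (10,000 runs per cell). The full-score column can be checked exactly: λ = N·(2/9)d²/[2(1 − r)]. For N = 186 and d = 0.25 this is 186 × 0.01389/0.70 = 3.69, giving power 38%.

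| Per arm | d | Full score | 25/25/25/25 | 16/34/34/16 | 10/15/25/50 |
|---|---|---|---|---|---|
| 62 | 0.25 | 38% | 28% | 29% | 22% |
| 62 | 0.4 | 79% | 62% | 64% | 48% |
| 62 | 0.5 | 94% | 80% | 83% | 65% |
| 62 | 0.6 | 99% | 93% | 94% | 79% |
| 47 | 0.25 | 29% | 22% | 22% | 17% |
| 47 | 0.4 | 65% | 49% | 50% | 37% |
| 47 | 0.5 | 85% | 69% | 71% | 52% |
| 47 | 0.6 | 96% | 83% | 86% | 66% |

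Before rounding, the losses in this table run from 4.6 to 16.3 points for the two even splits and from 11.8 to 32.8 for the skewed one. Separate runs with fewer repetitions differ by a point or so, hence about 4 to 17 and about 11 to 34. A more extreme split (5/10/25/60) loses more, up to about 42 points in the same set-up.

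Routes 2 and 3 attach different effects to d = 0.25, so their base powers differ. Losses should be compared within a route.

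**The case against.** The strongest reply is that the article describes the instrument and does not say that the four levels are the analysed variable. The sentence could describe a grouping used to interpret an underlying score, as the K6 severity groups do. The RM-ANOVA sentence is generic and cannot hold literally for every outcome: the help-seeking behaviour items are 0/1, app quality is rated once, and self-monitoring adherence is a single count. Multilevel models are also planned. The article gives no summary score for app quality, for credibility and expectation, or for help-seeking intentions, and a condensed article may leave such detail to the full protocol or SAP.

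Part of this stands. The intended variable is inferred from two sections, so certainty about it would be too strong. But for the PAM the scoring is not left open: a rule is given, and it is the coarse one. If a grouping for interpretation was meant, the sentence needs the same correction.

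A reader might go further and infer that at least 9 points of power are always lost, or that most true change disappears. Neither is supported. The loss is about 7 to 8 points at 47 per arm, d = 0.25 and even levels, and about 5 to 6 at 62 per arm and d = 0.6. About 44 to 54% of simulated participants show no change of level under the splits tabulated in the simulation, and across the splits examined 0.84 to 0.94 of the standardised effect is kept.

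**Conclusion.** The point holds as a specification weakness in one secondary outcome. Followed as written, the article analyses user activation as a four-category grade, and every scenario examined loses power. The size is about 4 to 17 points with fairly even levels and about 11 to 34 with skewed levels (10/15/25/50). It is conditional on assumed level frequencies, a normal underlying score, r = 0.65 carried over from the primary outcome, and d carried over (0.25) or assumed (up to 0.6). These ranges are illustrations and not bounds: a heavier pile-up in one level would cost more.

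A reader might infer that the trial's main conclusion or its sample size is in doubt. It is not. The K6 analysis and the totals of 141 and 186 do not depend on the PAM, and the article sets no power target for user activation.

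**What to change.** In Secondary Outcomes, under user activation, name the continuous PAM score (the sum or the scaled score over the 13 items) as the variable analysed, and state that the four levels are reported descriptively only. This costs one sentence and needs no further data, visits or participants. The Trial Status section says that recruitment has not begun, so the change can be made before any data exist.
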